#### *National registries, clinical database and medical records*

Clinical, prognostic and treatment factors will be obtained from the Danish Breast Cancer Cooperative Group (14). In order to develop cost-utility analyses, use of health services

including all outpatient visits to any healthcare clinic will be obtained from the local municipality rehabilitation centers, the Danish National Patient Registry (15) and medical records while information on disability and productivity loss (sick leave, disability pension and retirement pension) will be obtained from the Integrated Database for Labor Market Research (16). Further, information on national health service cost will be obtained from DRG costs from Statens Serum Institute. We will obtain information on disease characteristics (stage and tumor characteristics) and treatment (hospitalization, treatment type, municipality-based rehabilitation and dates for these) on their breast cancer as well as other diseases (diagnosis and date).

### Outcomes

Data collection instruments used to measure the individual outcomes are illustrated in Figure 2 and items for all questionnaires are shown in Appendix 10. The primary outcome is psychological distress, defined as a multifactorial, unpleasant psychological (cognitive, behavioural, emotional), social or spiritual emotional experience that potentially influences the ability to manage the cancer disease, symptoms and treatment. This will be measured using the distress thermometer. Secondary outcomes include anxiety and depression, breast cancer specific psychological and physical symptoms, quality of life measure to obtain cost-utility, health behaviour (smoking, alcohol consumption, body mass index and physical activity), fear of recurrence, social support, unmet needs, and acceptability. Feasibility outcomes will include indicators of whether the intervention has had an effect on the mechanisms and will include patient activation.

**Figure 2. Data collection instruments**

| Outcome            | Scale                   | Baseline before surgery | 3 week screening | 10 week screening | 18 week screening | 6 months follow-up | 12 months follow-up | 18 months follow-up |
|--------------------|-------------------------|-------------------------|------------------|-------------------|-------------------|--------------------|---------------------|---------------------|
| Demographics       | Single items            | X                       |                  |                   |                   |                    |                     |                     |
| Social support     | MOS                     | X                       |                  |                   |                   |                    |                     |                     |
| Distress           | DT                      | X                       | X                | X                 | X                 | X                  | X                   | X                   |
| Anxiety            | GAD 7                   | X                       | X                | X                 | X                 | X                  | X                   | X                   |
| Depression         | PHQ 9                   | X                       | X                | X                 | X                 | X                  | X                   | X                   |
| Symptoms           | FACT-B                  | X                       | X                | X                 | X                 | X                  | X                   | X                   |
| Physical function  | Physical function scale | X                       | X                | X                 | X                 | X                  |                     | X                   |
| Self-efficacy      | PAM                     | X                       |                  |                   |                   | X                  | X                   | X                   |
| Fear of recurrence | CARQ                    |                         |                  |                   |                   | X                  | X                   | X                   |
| Pain               | Single items            | X                       |                  |                   |                   | X                  | X                   | X                   |
| Neuropathy         | Single items            | X                       |                  |                   |                   | X                  | X                   | X                   |

|                    |              |   |  |  |  |   |   |   |
|--------------------|--------------|---|--|--|--|---|---|---|
| Sleep              | PSQI         | X |  |  |  | X | X | X |
| Cognitive function | FACT-cog     | X |  |  |  | X | X | X |
| Health behavior    | Single items | X |  |  |  |   |   | X |
| Need for support   | Single items | X |  |  |  | X | X | X |
| Quality of life    | EQ-5D        | X |  |  |  |   |   | X |
| Acceptability      | Single items |   |  |  |  |   |   | X |

Note. MOS Medical Outcomes Study Social Support Survey (17). DT Distress thermometer (18,19). GAD 7 Generalized Anxiety Disorder (20). PHQ 9 (depression) The Patient Health Questionnaire (21). FACT-B Functional Assessment of Cancer Therapy –Breast (22). Physical Function Scale (29). PAM Patient Activation Measure (23). CARQ Fear of Recurrence (24). Pain (single items), neuropathy (single items). PSQI Pittsburgh Sleep Quality Index (25). FACT-cog Functional Assessment of Cancer Therapy-Cognitive (26). Health behavior including smoking, alcohol, physical activity, BMI (single items). Need for support (single items). EQ-5D Euro Quality of Life-5-Dimensional Classification (27).

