| Inclusion            | Criteria include: Newly diagnosed with breast cancer (i.e. prior to surgery), scheduled for breast cancer surgery at Section of Breast Surgery at Rigshospitalet, 18 years or above, Danish citizen, read, understand and speak Danish, female gender, no severe cognitive problems or dementia, no severe psychiatric disease requiring treatment, e.g. schizophrenia, alcohol or narcotic dependence, has signed written informed consent. Those who experience high psychological distress (score $\geq 7$ on the distress thermometer) will enter the RCT whereas those who experience low psychological distress (score $< 7$ on the distress thermometer) will be followed in an observational questionnaire study. |
| Method               | During a 2-year period, 758 patients newly diagnosed with breast cancer will be recruited from the Section of Breast Surgery at Rigshospitalet, Copenhagen. Of these 324 participants enter the RCT and are randomized in a computer-generated sequence of 1:1 to the intervention (nurse-navigation) or control group (standard care). A total of 432 participants will enter an observational questionnaire study. All participants are followed for 1,5 years.                                                                                                                                                                                                                                                         |
| Intervention         | The intervention is a program of individually tailored nurse navigation for distressed breast cancer patients. The specific change objectives are to improve knowledge, social norms and self-efficacy so that the patient can self-manage or actively engage in professional rehabilitation to alleviate her psychological and physical symptoms. The intervention consists of systematic report of symptoms to the nurse and up to six individual, manual-based, face-to-face or telephone nurse navigator sessions depending on individual needs.                                                                                                                                                                      |

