### **DATA COLLECTION**

#### *Questionnaires*

Both the intervention and the control group will be assessed before surgery (T1) and 1 week (T2), 6 months (T5) and 12 months (T6) and 18 months (T7) after surgery. Patients randomized to the intervention group will also be assessed at 2 months (T3) and 4 months (T4). Patients who were not distressed (score < 7 on the distress thermometer) at T1 will be excluded from the trial but will be followed longitudinally in a sub-study by filling in questionnaires and with the same follow-up assessments as the control group. The questionnaires allow assessment of the primary and secondary outcomes and also covariates and mechanisms. The baseline questionnaire will be paper-based and filled out in the clinic. The follow-up questionnaires will be electronic and a secured link will be sent to the patient's e-mail address. The electronic platform will manage questionnaire invitations and reminders.

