## STATISTICAL ANALYSES

Descriptive analyses will provide information on inclusion, feasibility, including participation in intervention components and data collection, satisfaction with the intervention, and information on nurse management of symptoms from medical records. Analyses will be based on intention-to-treat, with t tests to compare mean differences in change in each group between baseline and 6, 12 and 18 months of follow-up and with mixed models including all follow-ups. Primary analyses will test the effect of the intervention on distress, and secondary analyses will test for psychological symptoms, physical symptoms, and health behaviour (smoking, alcohol, BMI, physical activity). The effect of the intervention in the control and the intervention group will be assumed to be normally distributed and will be tested by the F-test. In all analyses, 99% confidence intervals will be calculated. Analyses will be performed based on the intention to treat principle including all participants and in sensitivity analyses, imputations of missing data will be performed using the last-observation-carried-forward method (28). In analyses aiming to describe the clinical impact of the intervention, we will estimate how many percent of the cases of distress, anxiety, depression and physical symptoms in the intervention versus the control group will be moved to non-cases. Furthermore, in cost-utility analyses, we will apply quality adjusted life years (QALY) to weigh the life expectancy of a patient against the Euro Quality of Life 5-Dimensions Classification (5Q-5D). Using incremental analyses, mean differences in costs (health care +disability + productivity loss + intervention) are compared with mean differences in health consequences for the intervention versus the control group.

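### EQ-5D is collected only before surgery and at 18 months, so the QALY comparison cannot observe how any difference between the arms develops in between

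*Protocol*

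**What the plan says.** The Outcomes section of the protocol gives the role of the EQ-5D as "quality of life measure to obtain cost-utility". Statistical analyses then says that "we will apply quality adjusted life years (QALY) to weigh the life expectancy of a patient against the Euro Quality of Life" instrument, and that mean differences in costs "are compared with mean differences in health consequences for the intervention versus the control group". No other utility instrument is named, and there is no mapping from another scale to utilities.

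The schedule in Figure 2 has this row: "Quality of life | EQ-5D | X | | | | | | X". The table is broken across pages, but its columns can still be read. The sleep row in the same fragment is "Sleep | PSQI | X | | | | X | X | X", with marks at baseline, 6, 12 and 18 months. The blank EQ-5D cells at 6 and 12 months are therefore real.

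The synopsis states the horizon: "All participants are followed for 1,5 years". Under Questionnaires, "Both the intervention and the control group will be assessed before surgery" and again at 1 week, then at "6 months (T 5 ) and 12 months (T 6 ) and 18 months (T 7 ) after surgery". The 2- and 4-month assessments are for the intervention arm only. Follow-up questionnaires are electronic.

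**The concern.** A QALY difference is utility accumulated over time. With utilities only at the two ends of an 18-month period, everything between them has to be assumed. That interval holds the symptom screening (to 4 months after surgery), the navigation it informs, and the oncological treatment. Costs are to come from registers, municipal centres and medical records, which can be counted across all 18 months. Continuous costs would thus be set against one late utility contrast.

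The result matters for a decision. The Perspectives section makes the offer of implementation support to all Danish breast cancer departments depend partly on promising cost-effectiveness, and one of the four planned papers is on cost. In addition, a woman who does not return the 18-month form has no follow-up utility at all.

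**Working it through.** The protocol states no QALY, utility or cost-per-QALY figure, so there is nothing to reproduce. The check is how the two-point schedule behaves.

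**Inputs from the protocol**
- EQ-5D times: 0 and 1.5 years (Figure 2).
- Contacts shared by both arms at 0.5, 1 and 1.5 years (Questionnaires).
- Horizon T = 1.5 years (Synopsis).

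**Assumptions (not in the protocol)**
- QALYs are computed by the trapezoid rule over 18 months.
- The expected utility difference at baseline is 0, by randomisation.
- The short gap between the baseline form and surgery is ignored.
- The utility difference D and its course over time are hypothetical.

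**Two-point estimate.** 1.5 × (0 + D₁₈)/2 = 0.75 × D₁₈, whatever happens in between.

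**Sustained effect.** If the difference rises linearly to D by time a (in years) and then stays there, the true gain is D × (1.5 − a/2). With 6- and 12-month values added, the four-point estimate for any onset by 6 months is 0.5 × D/2 + 0.5 × D + 0.5 × D = 1.25D. For onset by 12 months the values are D/2, D and D, giving 0.125D + 0.375D + 0.5D = 1.00D.

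| Full effect reached | True gain | Two-point | Error | Four-point | Error |
|---|---|---|---|---|---|
| Immediately | 1.500D | 0.75D | −50% | 1.25D | −17% |
| By 1 month | 1.458D | 0.75D | −49% | 1.25D | −14% |
| By 4 months | 1.333D | 0.75D | −44% | 1.25D | −6% |
| By 6 months | 1.250D | 0.75D | −40% | 1.25D | 0% |
| By 12 months | 1.000D | 0.75D | −25% | 1.00D | 0% |

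The relative error does not depend on D. For onset by 6 months and D = 0.03, 0.05 or 0.10, the two-point estimates are 0.0225, 0.0375 and 0.0750, against true gains of 0.0375, 0.0625 and 0.1250. For a fixed cost difference, cost per QALY is overstated by 1/0.75 = 1.33 times (onset by 12 months) to 1/0.50 = 2.0 times (immediate onset).

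**Other courses**
- Peak D at 6 months, falling linearly to D/2 at 18 months: true 0.25D + 0.75D = 1.00D; two-point 0.75 × D/2 = 0.375D (about −62%).
- Peak D at 6 months, falling linearly to 0 at 18 months: true 0.25D + 0.50D = 0.75D; two-point 0 (−100%).
- No difference until 12 months, then rising to D at 18 months: true 0.5 × D/2 = 0.25D; two-point 0.75D (+200%).
- Linear growth over all 18 months: true 0.75D; two-point 0.75D (exact). Of the courses tried, this is the only one the two-point schedule gets right.

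**The case against.** The best counter-argument is that the protocol contains no error of calculation here and does not prescribe a straight line. It gives no interpolation rule and no explicit QALY horizon, and an analysis plan may settle both. PHQ-9, GAD-7, FACT-B and pain are collected in both arms at 6 and 12 months and could feed modelled utilities. This stands in part: the factor 0.75 is conditional on the usual method, and it would be too strong to say that nothing between the two points could ever inform the estimate. But no such model is specified, it would need outside assumptions, and no analysis rule recovers utilities that were not collected.

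Some stronger readings are tempting but not supported:
- A reader might infer that the QALY gain will be understated. The direction is not fixed: the courses tried run from −100% to +200%, and the protocol gives no utility effect, onset or fading pattern.
- A reader might infer that a fall in utility during treatment biases the comparison. A fall common to both arms cancels; only the course of the between-arm difference matters.
- A reader might infer that the plan requires quality of life to be tested at 6 and 12 months and then fails to collect it. Statistical analyses lists psychological symptoms, physical symptoms and health behaviour for its secondary tests, not quality of life. FACT-B, which the reference list describes as a quality-of-life instrument, is collected at both times.
- A reader might take the 20% allowance under Power and participation as the expected share of missing 18-month EQ-5D forms. It covers drop-out and missing data overall and was used to size the case to non-case comparison. Women lost before 6 months would gain nothing from the added forms.

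It is also fair to say that a four-point area is not the truth. The table shows that it still understates effects that begin well before 6 months.

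**Conclusion.** The point holds as a weakness of the measurement schedule in a secondary analysis. The primary distress outcome, its power and the symptom outcomes are untouched. The schedule itself is read directly from Figure 2. That the QALY difference becomes 0.75 times the 18-month utility difference follows if QALYs are taken as the area under the curve over 18 months with equal baselines. The percentages show how sensitive the result is to the course of the effect; they do not forecast the error in this trial. The case for change rests on the fact that the missing information cannot be restored at analysis and is cheap to collect.

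**What to change.** In Figure 2, add the EQ-5D at the 6- and 12-month follow-ups in both arms. In Statistical analyses, state that QALYs over 18 months are the area under each woman's utilities at baseline, 6, 12 and 18 months. State also that missing utilities are handled by multiple imputation or a mixed model that uses the observed 6- and 12-month values, not by carrying the last value forward or by shortening the horizon. Carry-forward is the only imputation the section now names, for sensitivity analyses. Under the present schedule it would extend a woman's pre-surgery utility across all 18 months.

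The cost is one short instrument in two electronic questionnaires that both arms already receive, a small extra burden on participants, and a schedule amendment. No extra visits or staff are needed. A smaller error remains for sustained effects that begin well before 6 months, about 6% to 17% in the cases tried.

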## STATISTICAL ANALYSES

Descriptive analyses will provide information on inclusion, feasibility, including participation in intervention components and data collection, satisfaction with the intervention, and information on nurse management of symptoms from medical records. Analyses will be based on intention-to-treat, with t tests to compare mean differences in change in each group between baseline and 6, 12 and 18 months of follow-up and with mixed models including all follow-ups. Primary analyses will test the effect of the intervention on distress, and secondary analyses will test for psychological symptoms, physical symptoms, and health behaviour (smoking, alcohol, BMI, physical activity). The effect of the intervention in the control and the intervention group will be assumed to be normally distributed and will be tested by the F-test. In all analyses, 99% confidence intervals will be calculated. Analyses will be performed based on the intention to treat principle including all participants and in sensitivity analyses, imputations of missing data will be performed using the last-observation-carried-forward method (28). In analyses aiming to describe the clinical impact of the intervention, we will estimate how many percent of the cases of distress, anxiety, depression and physical symptoms in the intervention versus the control group will be moved to non-cases. Furthermore, in cost-utility analyses, we will apply quality adjusted life years (QALY) to weigh the life expectancy of a patient against the Euro Quality of Life 5-Dimensions Classification (5Q-5D). Using incremental analyses, mean differences in costs (health care +disability + productivity loss + intervention) are compared with mean differences in health consequences for the intervention versus the control group.

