### ***Randomization***

Women who are distressed (score  $\geq 7$  on the distress thermometer) (N=324) will be included in the randomized controlled trial and randomized in a computer-generated sequence of 1:1 to the intervention or control group, with stratification by age ( $< 60$  and  $> 60$  years), generating a balanced number of random assignments to the two groups in blocks of randomly varying sizes of six, eight or ten patients securing an equal distribution of patients in both groups. The randomization is blinded. Thus, neither the investigators nor the patients can influence the group to which each patient is allocated. An electronic platform will be developed by an experienced IT consultant company, to register, randomize and track included patients. The same platform will be used for the intervention activities and data collection.

Immediately after randomization, the nurse will inform patients about group allocation and consequences for further study participation. The nurse will schedule the first appointment with the patients in the intervention group.

Women who are not distressed (score  $< 7$ ) (N=432), will participate in an observational group following the same procedure as the control group.

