**Figure 3. Percentage of women changing from cases to non-cases in intervention and control group**

| Control group (%) | Intervention group (%) |
|-------------------|------------------------|
|-------------------|------------------------|

|                         |    |    |
|-------------------------|----|----|
| Distress ( $\geq 7$ )   | 61 | 90 |
| Anxiety ( $\geq 8$ )    | 53 | 80 |
| Depression ( $\geq 8$ ) | 44 | 49 |

Conservatively, we expect slightly lowered differences in change from case to non-case in the large full-scale study (20 %), compared to those observed in the pilot study (30%).

In a 2-year period, we expect 948 women to fulfill the inclusion criteria. With an expected participation rate of 80% (85% was reached in the pilot study) 758 will participate. Of these 43% will have high distress (N=324) and will enter the RCT. 57% will have low distress (n=432) and will be invited to participate in observation group who will fill-out questionnaires.

Due to a large number of planned analyses in the RCT study, we assume a highly conservative alpha to be 1%. Within a 2-year inclusion period, we will include 324 patients and an estimated 20% will drop-out or have missing data, resulting in final sample of 260.

With 130 women in each group, an expected 61% women move from cases to non-cases on distress in the control group and 81% percent women move from cases to non-cases on distress in the intervention group, we will obtain 84% power. Similar calculations for anxiety and depression reveals power of 78% and 76%.

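### The protocol does not say whether change-score t tests or a mixed model is primary for distress; the t tests are valid but inefficient, so the mixed model, adjusted for baseline and age stratum, should be primary

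*Protocol*

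**What the plan says.** The protocol's Statistical analyses section names two analyses in one sentence. The first is given as "with t tests to compare mean differences in change in each group between baseline and 6, 12 and 18 months of follow-up". The second is added with the words "and with mixed models including all follow-ups". It makes distress the subject of the primary analyses but does not say which method is primary. A later sentence mentions an F-test without tying it to either method. The section also states "Analyses will be performed based on the intention to treat principle including all participants", and that in sensitivity analyses "imputations of missing data will be performed using the last-observation-carried-forward method". Confidence intervals are to be at 99%.

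The Randomization section says that women are "randomized in a computer-generated sequence of 1:1 to the intervention or control group", "with stratification by age" at 60 years. Neither the age stratum nor the baseline score is named as a covariate in any analysis. The Power and participation section expects that "an estimated 20% will drop-out or have missing data, resulting in final sample of 260".

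The Questionnaires section places common assessments before surgery (T1), at 1 week (T2), and at 6, 12 and 18 months (T5 to T7). The 2- and 4-month assessments (T3, T4) are for the intervention group only.

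**The concern.** Two methods for the primary outcome with no stated order leave open which result carries the conclusion. If it is the t tests, three features cost precision.

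- **Baseline.** A change score subtracts the baseline with a coefficient fixed at 1. Entry requires a distress score of 7 or more, so the baseline range is narrow and the true slope of follow-up on baseline may be well below 1. Subtraction then adds noise and over-corrects chance imbalance between the arms.
- **Stratum.** If age predicts distress, a t test that leaves out the randomisation stratum has a standard error that is too large.
- **Missing values.** A change at a given visit exists only for women with both values, and the plan itself expects 20% to drop out or have missing data.

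The mixed model as worded needs care too. A model over all follow-ups would take in T3 and T4, where the control group has no data to compare.

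**Working it through.** **The plan's own figure.** Inputs from Power and participation: 130 per arm, 61% against 81% moving from case to non-case, alpha 1% (sidedness not stated; two-sided used here).

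- Pooled rate 0.71. Standard error under the null: sqrt(2 × 0.71 × 0.29 / 130) = 0.0563.
- Standard error under the alternative: sqrt((0.61 × 0.39 + 0.81 × 0.19) / 130) = 0.0549.
- Power = Φ((0.20 − 2.576 × 0.0563) / 0.0549) = Φ(1.00) = 84.2%, against 84% stated.

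The figure is reproduced. It is for a difference in proportions, so it describes neither the change-score t test nor the mixed model.

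**Change score against baseline adjustment.** Let s1 and s2 be the baseline and follow-up standard deviations, r their correlation, and k = s1/s2.

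- Change-score variance: s1² + s2² − 2·r·s1·s2.
- Baseline-adjusted variance: s2²(1 − r²).
- The difference is (s1 − r·s2)². It is never negative, and it is zero only when the slope r·s2/s1 equals 1.
- Ratio, adjusted over change: (1 − r²) / (1 + k² − 2rk). With k = 1 this is (1 + r)/2.

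The protocol gives no s1, s2 or r, so every row below rests on assumptions.

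| Assumed setting | r | Variance ratio |
|---|---|---|
| Distress, s1 = 1, s2 = 2.5 (k = 0.4) | 0 / 0.1 / 0.2 / 0.4 | 0.862 / 0.917 / 0.960 / 1.000 |
| Baseline SD half the follow-up SD (k = 0.5) | 0.3 / 0.5 / 0.7 | 0.958 / 1.000 / 0.927 |
| Simulated bivariate normal, baseline cut to its top 43% (the share the protocol expects at 7 or more) | 0.3 / 0.5 / 0.7 before the cut | 0.851 / 0.902 / 0.945 |
| Equal SDs (k = 1) | 0.3 / 0.5 / 0.7 | 0.65 / 0.75 / 0.85 |

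Example: k = 0.4, r = 0.2 gives 0.96 / (1.16 − 0.16) = 0.960. The slope there is 0.2 × 2.5 / 1 = 0.5, so the change score corrects a chance baseline imbalance by twice what the regression supports.

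The standard error falls by 1 − sqrt(ratio). That is about 8%, 5% and 3% in the simulated truncated setting, and about 19%, 13% and 8% with equal SDs.

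**Cost of adjusting.** A t test on 260 women has 258 residual degrees of freedom. Baseline and stratum take two: 258/256 = 1.008, under 1% of variance.

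**Missing data.** 324 × 0.8 = 259.2, which agrees with the planned 260. A likelihood-based mixed model also keeps women with some but not all follow-ups. How many they are cannot be derived from the protocol.

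**Which outcomes can be modelled this way (Figure 2).** Fear of recurrence (CARQ) and acceptability have no baseline. Health behaviour and EQ-5D are marked only at baseline and 18 months. Physical function has no 12-month mark.

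**The case against.** The strongest reply is that a mixed model is already planned, that its covariates are commonly left to a statistical analysis plan, and that none is shown here. That stands as far as it goes: silence on the mixed model's covariates is not in itself an error. The unadjusted change-score t tests, however, are a method the protocol states, and it does not subordinate them to the model.

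A reader might infer several stronger things that the documents do not support.

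- *That the plan discards women with missing data, against its intention-to-treat statement.* This describes only the t-test half. The mixed model keeps women with partial follow-up, and last observation carried forward is planned as a sensitivity analysis. The recommended model does not recover women with no follow-up at all either.
- *That the t tests ignore baseline.* They use it, with the coefficient fixed at 1.
- *That the t tests are biased.* Under 1:1 randomisation they are valid. Leaving out the stratum makes them, if anything, conservative.
- *That the loss is large, or affects every outcome.* With equal SDs and r = 0.5 the gain is worth 1/0.75 = 1.33, a third more patients, but that is one assumed point. At r = 0.7 it is 1/0.85 = 1.18. For distress the gain is smaller and vanishes where the slope is 1. Outcomes without a baseline gain nothing from the baseline term.
- *That the 84% power is wrong or would rise.* It is for proportions and is untouched.

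**Conclusion.** The point holds as one of efficiency and clarity, not validity. The protocol leaves open which of two analyses is primary for distress, and one of them is less precise than a model that uses data already collected.

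Under the assumed inputs, the adjusted variance is about 0.85 to 1.00 of the change-score variance for distress. It is about 0.65 to 0.85 for outcomes with equal standard deviations and correlation 0.3 to 0.7. No size can be put on the gain from the age term. Asymptotically, adjustment for baseline does no worse than the change score.

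A separate, minor slip affects the same factor: the strata are given as "with stratification by age ( $< 60$ and $> 60$ years", which leaves a woman aged exactly 60 in neither.

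**What to change.** 1. State that the planned mixed model is the primary analysis. Fit it at the post-baseline visits common to both arms (for distress: 1 week, 6, 12 and 18 months), leaving out T3 and T4. Include arm, visit, arm-by-visit, baseline score (by visit) and age stratum.
2. Report the adjusted differences at 6, 12 and 18 months from this model with 99% confidence intervals. Make the change-score t tests supportive or drop them.
3. For secondary outcomes, include the baseline term only where a baseline is collected, so not for CARQ or acceptability. Use a single-visit ANCOVA for outcomes measured only at baseline and 18 months (health behaviour, EQ-5D). Report physical function only at the common visits where it is measured.
4. Define the age strata so that exactly 60 falls in one of them, and check that this matches how the randomisation platform assigns such women.

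The cost is wording and, in the analysis, one or a few degrees of freedom with about 260 women. No further data are needed.
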